### 2.5. Quantitative Sensory Testing (QST)

For quantitative sensory testing, the pressure pain threshold (PPT) will be measured with an electronic algometer (Somedic AB, Sösdala, Sweden). The probe area will be 1cm^2^, and the force will increase at a rate of approximately 30 kPa/s. Patients will be seated comfortably for hand and leg measurements or lying on their non-tested side for temporalis muscle assessments. They will be instructed to press a stop button as soon as they perceive a change from pressure to pain. To familiarize patients with the procedure, a training test will be conducted on a neutral body part before measurements begin. PPT will be measured three times at each assessment site, and the average value will be used for analysis.

PPTs will be assessed in the trigeminal area over the anterior column of the temporalis muscle. Since previous studies showed no side-to-side differences in PPT over the trigeminal area in migraine patients with unilateral migraine [41], measurements will be taken on the symptomatic side for unilateral migraine cases and on the dominant side for patients with bilateral or shifting-side migraines.

PPTs will be also assessed in the extra-trigeminal area over the second metacarpophalangeal joint of the dominant hand and over the tibialis anterior muscle of the dominant side to evaluate widespread pressure pain hypersensitivity. These sites are commonly used to assess widespread hyperalgesia as a sign of central sensitization in chronic pain conditions [42]. Studies have shown that migraine patients exhibit lower PPTs in the trigeminal, cervical, second metacarpal, and tibialis anterior regions compared to healthy individuals [43]. However, a recent systematic review suggested that migraine patients have lowered PPTs in local areas but not in non-local areas [44].

Wind-up refers to the progressive increase in the excitability of trigeminal and spinal dorsal horn wide dynamic range neurons (WDRs) evoked by repetitive identical (same frequency) stimulation of primary afferent nociceptive C-fibers (homosynaptic potentiation) [45]. The human equivalent of this phenomenon is temporal summation, which manifests as an increased pain perception with repetitive, constant nociceptive stimulation. To assess temporal summation, the wind-up ratio (WUR) will be calculated. Mechanical pin-prick-evoked pain will be tested using a 50.1 g device (Aalborg University, Aalborg, Denmark) over the anterior column of the temporalis muscle. The symptomatic side will be assessed for unilateral migraine patients, while the dominant side will be used for bilateral or shifting-side migraine cases. Patients will lie on their non-tested side and rate their pain on a 0–10 scale for both the first and last of 10 identical stimuli applied at the same location on the temporalis muscle at a frequency of 1 stimulus per second. The difference between the last and first pain ratings will be calculated, with a positive WUR indicating increased temporal summation [46].

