### 2.3. Randomization, Schedule, and Adherence

Patients will be randomly assigned at a 1:1 ratio using a pre-generated randomization list created in SPSS by an experimenter who will not be involved in patient recruitment, treatment, or data analysis. Participants will be required to attend a full course of 10 lessons, with the first and last sessions conducted in person and the remaining eight delivered remotely via PowerPoint presentations. Lessons will be held in small groups, with the real and control education groups scheduled on different days to prevent interaction between participants from different study arms. The treatment will be considered valid if patients attend at least 8 out of 10 lessons. In case of absence, the PowerPoint presentation from the missed session will be sent to the participant. Additionally, a brief Q&A session will be conducted before the next lesson to review the content and address any questions.

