### 2.6. Nociceptive Blink Reflex (nBR)

The nBR will be recorded using a previously established setup for migraine research [28]. Electrical stimulation will be applied via an electrode placed near the right supraorbital foramen. Two pairs of recording electrodes will be placed bilaterally over the orbicular oculi muscle: the active electrode over the inferior portion and the reference electrode on the lateral part. A ground electrode will be placed on the nose. Recordings will be conducted at a sampling rate of 5000 Hz and a sweep duration of 150 ms. A 0.2 ms square wave with an ascending-descending sequence with 0.2 mA of intensity steps will be used to probe stimulation. Both the perception threshold (the intensity at which the patient detects at least 50% of the stimuli) and pain threshold (the intensity at which the patient reports pain in at least 50% of the stimulations) will be determined for each subject. During the recording, stimuli will be delivered at 1.5 times the pain threshold to minimize habituation over time. The inter-stimulus interval will be pseudo-randomized between 15 and 17 s. Ten rectified EMG responses will be recorded and averaged offline, with the first response of each nBR discarded to eliminate startle contamination. The amplitude of the R2 reflex response will be quantified as the value of the area under the curve (AUC). To minimize variability, the AUC will be normalized for stimulation intensity (according to the formula AUC/i^2^), as recommended [47].

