### 2.7. Intensity Dependence of Auditory Evoked Potentials (IDAP)

IDAP recordings will be conducted following established protocols [27,48,49]. Auditory evoked potentials will be delivered at four different intensities (60, 70, 80, 90 dB) in a pseudo-randomized order. For each intensity, 90 stimuli will be delivered. The sampling rate will be set at 4000 Hz and sweep duration at 400 ms (including 50 ms before and 350 ms after stimulus onset). Traces will be filtered offline with a 1–20 Hz pass-band filter. N1 will be identified as the most negative deflection occurring between 60–150 ms, while P2 will be defined as the most positive deflection between 120–200 ms. After removing electroencephalographic traces contaminated by artifacts, N1P2 peak-to-peak amplitudes will be measured and averaged for each intensity level. The IDAP slope will be modeled as a linear function interpolating the N1P2 amplitudes across the four intensity levels, with the slope value (μV/10 dB) representing the degree of IDAP.

Since this study involves patients with CM, neurophysiological and clinical evaluations will not be conducted during a strictly “interictal” period. Instead, assessments will take place at least 48 h after a migraine attack (defined as an episode with pain intensity >7/10, nausea, or marked photophobia).

Patients will be contacted two days post-assessment to verify whether any migraine attacks occurred within that period. Additionally, patients must refrain from using analgesics, triptans, or other rescue medications for at least 24 h before the assessment.

Recordings will be performed using a Natus Nicolet Edx system (Middleton, WI, USA).

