### 2.10. Plans for Analysis

An a priori calculation of the sample size was performed based on the primary endpoint. In line with studies on CM with MOH, we aim for a between group difference of 3.0 monthly headache days at T4 and a standard deviation of 4.5 [55]. Using an alpha error of 5%, a power of 80%, and a medium effect size, the calculated sample size is 70 patients. Considering a reasonable dropout rate, we plan to recruit 80 patients.

To assess the treatment’s effects on clinical and instrumental outcomes, a generalized linear mixed model for repeated measures (*p*-value < 0.05) will be performed on the primary outcome and, in a sub-analysis, on secondary outcomes. The model will include group and time as fixed effects, time by group as an interaction term, and the outcome as the dependent variable. Covariates will be selected from those identified as significantly different between groups [10]. A correlation analysis will also be conducted between migraine disability indexes and clinical/neurophysiological measures to identify potential biomarkers. False discovery rate correction will be applied to reduce type-I errors.

The number of adverse events (AEs) during the treatment period will be counted separately for the TNE-A and CON-A groups and classified according to common terminology criteria for adverse events (CTCAEs). An AE is defined as any adverse medical event associated with the use of a treatment in humans, regardless of whether it is considered related to the treatment. Causality (relationship to study treatment), action taken, and outcome will be summarized separately.

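### As described, wind-up rests on one unrepeated pin-prick series while PPT, nBR and IDAP are averaged, so it carries avoidable noise and may lose substantial power as a predictor, above all as a T1-to-T2 change

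*Protocol article*

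**What the plan says.** Section 2.5 of the protocol article sets out the wind-up test in detail: the device, the temporalis site, the side, the posture, 10 stimuli at one per second, and a 0-10 pain rating of the first and the tenth. The score follows: "The difference between the last and first pain ratings will be calculated". The article calls this a ratio, but it is a difference. It mentions one series and no averaging.

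The other markers are treated differently:

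- PPT, in the same section: "PPT will be measured three times at each assessment site, and the average value will be used for analysis".
- nBR, Section 2.6: "Ten rectified EMG responses will be recorded and averaged offline", with the first response discarded.
- IDAP, Section 2.7: "For each intensity, 90 stimuli will be delivered", and amplitudes are averaged within each intensity before the slope is fitted.

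Section 2.4 places QST at T1 and again at T2. Secondary endpoint (iii) in Section 2.2 compares the biomarkers between responders and non-responders and correlates them with the reduction in headache days. The Introduction names mid-treatment change in QST as a hypothesised early marker of benefit.

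**The concern.** A difference of two single ratings takes in the error of both, and a change between two visits takes in the error of four. Random error in a predictor pulls its observed correlation with outcome towards zero. Wind-up is the trial's only measure of temporal summation and the only one of these markers for which no averaging is described. The form of it that matters most to the hypothesis, the early change, is also the noisiest. If wind-up shows no association, the trial could not tell a marker that does not predict from one that was measured too coarsely. This is an acquisition rule, so an analysis plan cannot repair it afterwards: a series that was never repeated cannot be averaged.

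**Working it through.** **The plan's own figure.** No reliability, SD, effect size or power is stated for wind-up. The only sample size is for headache days: "Using an alpha error of 5%, a power of 80%, and a medium effect size, the calculated sample size is 70 patients", based on a difference of 3.0 and an SD of 4.5. For two arms at two-sided 5% and 80% power, n per arm = 2 × (1.960 + 0.842)² × 4.5² / 3.0² = 35.3, so 70.6 in total, or 72 after rounding up per arm. The 70 is reproduced to within two patients, but it says nothing about wind-up. I use it only as the number analysed.

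**Inputs.**
- From the document: N = 70; two ratings per assessment; assessments at T1 and T2 (Section 2.4; the Abstract says T0 and T2, and I follow Section 2.4).
- Assumed: true correlation with headache-day reduction 0.40; true between-patient SD of wind-up 1.0 or 1.5 points; true SD of the change 1 point; error SD of one rating s = 0.7, 1.0 or 1.5 points; a rounding variance of 1/12 per rating; independent errors between ratings and between series; all patients pooled; two-sided 5% with no false discovery rate adjustment.

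**Formulas**, for k averaged series:
- Error variance of the T1 score: 2(s² + 1/12)/k. Error variance of the change: 4(s² + 1/12)/k.
- Reliability = true variance / (true variance + error variance).
- Observed correlation = 0.40 × √reliability.
- Power from Fisher's z, with standard error 1/√67.

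**Worked case:** T1 value, true SD 1.5, s = 1.0. Error variance = 2 × 1.083 = 2.167. With one series, reliability = 2.25/4.417 = 0.51, observed correlation 0.285, power 67%. With three, error variance = 0.722, reliability 0.76, observed correlation 0.348, power 84%.

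| Score | True SD | s | Reliability, 1 → 3 series | Power, 1 → 3 series |
|---|---|---|---|---|
| T1 value | 1.5 | 0.7 | 0.66 → 0.85 | 79% → 89% |
| T1 value | 1.5 | 1.0 | 0.51 → 0.76 | 67% → 84% |
| T1 value | 1.5 | 1.5 | 0.32 → 0.59 | 48% → 74% |
| T1 value | 1.0 | 0.7 | 0.47 → 0.72 | 63% → 83% |
| T1 value | 1.0 | 1.0 | 0.32 → 0.58 | 46% → 73% |
| T1 value | 1.0 | 1.5 | 0.18 → 0.39 | 28% → 55% |
| Change | 1.0 | 0.7 | 0.30 → 0.57 | 45% → 72% |
| Change | 1.0 | 1.0 | 0.19 → 0.41 | 30% → 57% |
| Change | 1.0 | 1.5 | 0.10 → 0.24 | 18% → 37% |

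A perfectly reliable score would have 93% power under the same assumptions.

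**Sensitivity to the assumptions.**
- *Correlated errors within a series.* If the errors of the first and tenth ratings correlate at 0.5, the worked T1 case becomes 79% → 89%, so the gain falls from 17 to 10 points. The change at s = 1.0 becomes 45% → 72%: it starts higher, with about the same gain.
- *Day-to-day variation.* If half the error varies by day and repeats cannot remove it, the change rows become 45% → 56%, 30% → 39% and 18% → 23%. A T1 value with single-series reliability 0.5 goes from 66% to 75%.
- *A reliable single series.* At reliability 0.7 the T1 value goes from 81% to 90%; at 0.9, from 91% to 93%. With s = 0.5, true SD 2 and a true T1-T2 correlation of 0.5 to 0.7, the change goes from 82-87% to 90-91%.

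**The case against.** The article nowhere says that only one series is applied. That is inferred from silence in a condensed report that cites a source for the method, and markers of different kinds need not be replicated equally. This has some force. However, the article gives the repeat count for every other marker, including PPT in the same section, and describes the wind-up test down to posture and stimulus rate. One series is the natural reading, and anyone following the text would do that.

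A reader might infer more than the text supports:

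- *That wind-up loses much of its power.* Every SD, reliability and correlation above is assumed. If a single series is reliable, the T1 value loses little.
- *That a real predictor would probably be missed.* For the T1 value, three of the six scenarios have one-series power above 50%. The statement fits the change under the tabulated assumptions, but not under the more favourable ones.
- *That the error variance is necessarily doubled.* This needs independent errors. Two ratings about ten seconds apart in the same patient may share error that cancels in the difference.
- *That ratings are whole numbers.* Only a 0-10 scale is stated, so the rounding term is an assumption. It is small: without it the worked case is 69% → 85%.

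Repeats also have a cost of their own. Wind-up is, by the article's own account, a response that grows under repeated stimulation, so an earlier series could carry over into the next. None of this removes the precision gain where errors are at least partly independent between series.

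**Conclusion.** The point holds as a low-severity, inexpensive improvement. Wind-up as described is the one unaveraged marker among those in secondary endpoint (iii), and averaging raised power in every scenario tried. The direction needs only that errors are partly independent between series and that carry-over is limited. The size is not established by the documents. Across the tabulated assumptions, three series instead of one add about 10 to 27 points of power for the T1 value and about 20 to 27 for the change; the gain shrinks to a few points where a single series is already reliable or much of the error is day-level. The false discovery rate correction in Section 2.10 would lower all the power figures. The primary endpoint, the treatment comparison and the sample size are not affected.

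**What to change.** In Section 2.5, state that the 10-stimulus series is applied three times at the temporalis site at both T1 and T2. Separate the series by a fixed rest whose length is written down, is long enough to limit carry-over and is the same at both visits. Use the mean of the three last-minus-first differences as the score, as is already done for PPT. Record each series separately, so that carry-over and between-series reliability can be checked and the first series stays comparable with any patient already measured once.

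The cost is two more series, that is 20 more pin-pricks and a few minutes, at each of two existing visits, with the same device and assessor. The remaining risk is carry-over between series. If a single series is kept, say so outright and report the reliability of the single-series score next to any null result.

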### 2.6. Nociceptive Blink Reflex (nBR)

The nBR will be recorded using a previously established setup for migraine research [28]. Electrical stimulation will be applied via an electrode placed near the right supraorbital foramen. Two pairs of recording electrodes will be placed bilaterally over the orbicular oculi muscle: the active electrode over the inferior portion and the reference electrode on the lateral part. A ground electrode will be placed on the nose. Recordings will be conducted at a sampling rate of 5000 Hz and a sweep duration of 150 ms. A 0.2 ms square wave with an ascending-descending sequence with 0.2 mA of intensity steps will be used to probe stimulation. Both the perception threshold (the intensity at which the patient detects at least 50% of the stimuli) and pain threshold (the intensity at which the patient reports pain in at least 50% of the stimulations) will be determined for each subject. During the recording, stimuli will be delivered at 1.5 times the pain threshold to minimize habituation over time. The inter-stimulus interval will be pseudo-randomized between 15 and 17 s. Ten rectified EMG responses will be recorded and averaged offline, with the first response of each nBR discarded to eliminate startle contamination. The amplitude of the R2 reflex response will be quantified as the value of the area under the curve (AUC). To minimize variability, the AUC will be normalized for stimulation intensity (according to the formula AUC/i^2^), as recommended [47].

### 2.7. Intensity Dependence of Auditory Evoked Potentials (IDAP)

IDAP recordings will be conducted following established protocols [27,48,49]. Auditory evoked potentials will be delivered at four different intensities (60, 70, 80, 90 dB) in a pseudo-randomized order. For each intensity, 90 stimuli will be delivered. The sampling rate will be set at 4000 Hz and sweep duration at 400 ms (including 50 ms before and 350 ms after stimulus onset). Traces will be filtered offline with a 1–20 Hz pass-band filter. N1 will be identified as the most negative deflection occurring between 60–150 ms, while P2 will be defined as the most positive deflection between 120–200 ms. After removing electroencephalographic traces contaminated by artifacts, N1P2 peak-to-peak amplitudes will be measured and averaged for each intensity level. The IDAP slope will be modeled as a linear function interpolating the N1P2 amplitudes across the four intensity levels, with the slope value (μV/10 dB) representing the degree of IDAP.

Since this study involves patients with CM, neurophysiological and clinical evaluations will not be conducted during a strictly “interictal” period. Instead, assessments will take place at least 48 h after a migraine attack (defined as an episode with pain intensity >7/10, nausea, or marked photophobia).

Patients will be contacted two days post-assessment to verify whether any migraine attacks occurred within that period. Additionally, patients must refrain from using analgesics, triptans, or other rescue medications for at least 24 h before the assessment.

Recordings will be performed using a Natus Nicolet Edx system (Middleton, WI, USA).

### 2.8. Therapeutic Neuroscience Education

QST provides insight into the overall state of central nervous system (CNS) sensory amplification. It is typically conducted by applying peripheral stimuli (e.g., electrical, mechanical, thermal, or vibratory) and evaluating the CNS response. For this reason, QST is considered an indirect measure of sensory processing [50].

Studies have demonstrated that QST can predict chronic pain trajectories, assess the risk of pain chronification, and determine treatment outcomes [51].

Different QST modalities have been extensively investigated in migraine patients since the 1950s [34], yet significant heterogeneity remains in assessment methods. A recent systematic review with meta-analysis on QST in migraine patients concluded that alterations in somatosensory function in migraine are specific to the stimulus modality, measurement approach, and anatomical location [52].

The content of the program in the TNE-A group will align with established literature on the topic adapted from “Explain Pain” and “Explain Pain Supercharged” [53,54]. The TNE intervention will consist of ten one-hour group lectures delivered over a 10-week period. Groups will be composed of a moderate number of participants (4 to 8 individuals) to encourage interaction and participant feedback. The program will be administered by two dedicated experts, both of whom underwent standardized training by the same specialist to ensure consistency and reliability in the intervention, as supported by findings from an unpublished pilot feasibility study.

The TNE intervention will be delivered as follows. Initially, we will introduce a simple definition of pain according to the International Association for the Study of Pain and provide an overview of neuron functions, neuroanatomy, and pain classification (e.g., neuropathic, nociceptive, nociplastic). We will then discuss the origins of pain, addressing common misconceptions (e.g., nociception equals pain, pain intensity directly correlates with injury) and challenge migraine-specific misunderstandings (e.g., the belief that effective treatment must eliminate pain rather than promote significant clinical improvement). This will aim to facilitate a reconceptualization of pain for the patients. Next, we will explore pain modulation and the existence of descending/ascending and facilitator/inhibitory pathways underlying the role of our “internal pharmacy”. Patients will learn about the influence of feelings, thoughts, emotions, and beliefs on pain perception. Practical examples, scientific papers, and self-analysis will be used to demonstrate how various factors can impact pain experience. Metaphors such as “the brain as a protectometer” and “the brain as a spam filter” will be introduced to clarify these concepts. We will then explain what happens when pain becomes chronic and the key elements that facilitate chronicity. We will explain the concepts of central sensitization and brain plasticity, which are very important concepts in chronic pain patients. It is crucial for patients to understand that “the brain is trainable, and pain chronicity can be modulated by the brain” and that “we can teach our brain to re-activate its protective mechanisms” to foster clinical improvement. The later sessions will focus on how context and communication influence pain experience, particularly the placebo and nocebo effects and the role of positive language (“good words”). Stress management techniques will also be covered, considering that stress can trigger migraine attacks. Helping patients manage stress effectively will enable them to focus on the present moment, become aware of their thoughts, and accept them without judgment. The final session will recap the key points discussed throughout the previous nine sessions and emphasize the importance of lifestyle modifications and long-term management strategies for migraine control.

The program in the CON-A group will also consist of ten learning sessions, but instead of focusing on the individual–pain interaction, it will cover the following topics: the classification of headaches according to the ICHD-3 criteria; an overview of migraine, including its definition, symptoms, epidemiology, and genetics; migraine pathophysiology, where we will explain both mechanisms leading to pain during an attack and those that contribute to the recurrence of migraine attacks over time; a biomedical model of pain (explaining the association between tissue damage/inflammation and pain perception); the definition of chronic migraine, the mechanisms of migraine chronification, and how migraines can revert to an episodic form; an explanation of the prodromal and postdromal phases of migraine as well as trigger factors; a discussion on the classes of medications used in migraine management and general information on treatment strategies; the role of passive interventions in pain management; and a look at migraine comorbidities as well as the anatomy and biomechanics of the cervical spine. The final session will be a summary of the key points discussed in the previous nine sessions.

In both groups, patients will be assigned homework between sessions, primarily consisting of cognitive exercises such as reflecting on the material covered or explaining the concepts they learned to someone else in simple terms. This approach will help patients mentally organize the new information, reinforcing their understanding and retention of these concepts.

